## Abstract

**Background:**

Given the high prevalence of Cluster-C Personality Disorders (PDs) in clinical populations, disease burden, high societal costs and poor prognosis of comorbid disorders, a major gain in health care can be achieved if Cluster-C PDs are adequately treated. The only controlled cost-effectiveness study published so far found Individual Schema Therapy (IST) to be superior to Treatment as Usual (TAU). Group ST (GST) might improve cost-effectiveness as larger numbers can be treated in (>50%) less time compared to IST. However, to date there is no RCT supporting its (cost-) effectiveness. The overall aim of this study is to assess the evidence for GST for Cluster-C PDs and to improve treatment allocation for individual patients. Three main questions are addressed: 1) Is GST for Cluster-C PDs (cost-)effective compared to TAU? 2) Is GST for Cluster-C PDs (cost-) effective compared to IST? 3) Which patient-characteristics predict better response to GST, IST, or TAU?

**Methods:**

In a multicenter RCT, the treatment conditions GST, IST, and TAU are compared in 378 Cluster-C PD patients within 10 sites. GST and IST follow treatment protocols and are completed within 1 year. TAU is the optimal alternative treatment available at the site according to regular procedures. Severity of the Cluster-C PD is the primary outcome, assessed with clinical interviews by independent raters blind for treatment. Functioning and wellbeing are important secondary outcomes. Assessments take place at week 0 (baseline), 17 (mid-GST), 34 (post-GST), 51 (post-booster sessions of GST), and 2 years (FU). Patient characteristics predicting better response to a specific treatment are studied, e.g., childhood trauma, autistic features, and introversion. A tool supporting patients and clinicians in matching treatment to patient will be developed. An economic evaluation investigates the cost-effectiveness and cost-utility from a societal perspective. A process evaluation by qualitative methods explores experiences of participants, loved ones and therapists regarding recovery, quality of life, and improving treatment.

**Discussion:**

This study will determine the (cost-)effectiveness of treatments for Cluster-C PDs regarding treatment type as well as optimal matching of patient to treatment and deliver insight into which aspects help Cluster-C-PD patients recover and create a fulfilling life.

**Trial registration:**

Dutch Trial Register: NL9209. Registered on 28-01-2021,

**Supplementary Information:**

The online version contains supplementary material available at 10.1186/s12888-022-04248-9.

## Background

Cluster-C personality disorders (PDs; avoidant, dependent, and obsessive-compulsive) are characterized by severe anxiety, (interpersonal) dysfunction and maladaptive coping in dealing with PD-specific fears, such as avoidance and excessive control. The prevalence of Cluster-C PDs is 6.7% in the Western adult population [1] and 5% in the global population [2]. In clinical samples, Cluster-C PDs are estimated at a prevalence between 10.5% (for obsessive compulsive) and 24.6% (for avoidant) [3], and are associated with high comorbidity, notably social anxiety, eating disorders and depression [4].

Unsurprisingly, Cluster-C PDs impair quality of life, visible in decreased psychological well-being and impaired social relationships [5]. It has been found that individuals with Cluster-C PDs are impeded in marital status, educational achievements, and are more often economically inactive than individuals without PD [6, 7]. The latter is reflected in the fact that PDs are related to high economic costs in comparison to for instance depression or generalized anxiety disorder [8]. The annual cost of PDs in Europe is estimated at 27.3 billion euros [9]. For Cluster-C PD costs in the Netherlands are estimated between 12,000 and 13,500 euros per person per year (in 2007 prices) [10] and consist of elevated health costs, patient and family costs, productivity losses, and costs in other sectors. The total economic losses for this population may be even higher considering the difficulty to assess certain costs, such as loss of production due to excessive perfectionism, problems in cooperating with colleagues, and difficulties with fulfilling the role of parent [4].

Despite the high prevalence and the severe impact of Cluster-C PDs on individuals and society, there is a relative lack of attention in the scientific field to Cluster-C PDs in general and their treatment in particular. This scarcity of research on Cluster-C PDs is in part responsible for a lack of international guidelines concerning its treatment [11]. The absence of clear guidelines for adequate treatment might explain why the average number of previous treatments for Cluster-C PD patients was 2.33, with an average total duration of 2.67 years in one previous study on individual Schema Therapy (IST [12];). In addition, having a comorbid Cluster-C PD negatively affects the prognosis for other disorders and strongly predicts future functioning [4]. Considering the serious mental distress, dysfunction, and societal costs associated with Cluster-C PDs, more research into effective treatment is vital.

So far, the only treatment for Cluster-C PDs of which the (cost-)effectiveness was appropriately investigated (i.e., with a randomized controlled trial; RCT) is IST. A large Dutch RCT demonstrated superiority of IST to Treatment as Usual (TAU) for 6 PDs, of which >90% were Cluster-C [10, 12]. One year after completing IST, approximately 80% of patients recovered from their PD. ST assumes that maladaptive schemas can arise when a child's basic needs are not met and that these schemas underlie personality pathology [13, 14]. Central to contemporary ST are schema modes, which are defined as momentary states of mind which control the individual’s thinking, feeling, and acting at that moment. Dysfunctional schema modes can arise through the combination of maladaptive schemas and coping style and often had a functional role in childhood but became maladaptive in adulthood. Through the use of the therapeutic relationship (limited reparenting) and different techniques (including experiential ones), ST aims to reduce maladaptive and strengthen functional schemas and schema modes. Frameworks and specific schema mode models are available for Cluster-C PDs, showing the most common schema modes for avoidant, dependent and obsessive-compulsive PD, and the associated recommended treatment strategy [15].

A popular and economically attractive form of ST is group treatment, as larger numbers can be treated in less therapist time than with individual therapy (>50%), making it potentially more cost-effective than IST. In addition, the group format might offer extra therapeutic advantages such as support and understanding from group members which can help patients gain a sense of belonging and can facilitate secure attachment. Possibly group therapy would be exposure in itself for patients with cluster-c PD, where social avoidance and dependence play a major role in their pattern of symptoms. Furthermore, group therapy can induce vicarious learning and offer in vivo opportunities to practice with setting boundaries and expressing one's needs in a healthy way [16]. Group schema therapy (GST) has proven to be an effective treatment for borderline PD [17, 18] and was found superior to TAU [19, 20]. Only two studies have investigated GST for Cluster-C PD. First, a modest pilot study of a GST-protocol including 8 patients with mixed personality disorders (6 patients with avoidant PD and 2 with borderline PD) showed significant decline in avoidant PD symptom severity at follow-up [21]. The two patients with borderline PD were both reported as dropout, suggesting that mixing different PDs within this GST-protocol may be contra indicative. Second, a larger pilot study investigated our current GST-protocol in a multicenter open trial (9 sites, 137 patients). The treatment was highly acceptable: only 16 dropouts (11.6%). The decrease in symptoms from baseline to follow-up of the primary PD was large (effect sizes ranged from cohen’s d = .59 for obsessive compulsive PD, d = 1.33 for avoidant PD and, d = 1.52 for dependent PD).

It is likely that some patients are better off with individual (schema) therapy compared to group ST or TAU. Matching treatment to patient (personalized care) also reduces societal costs and demoralization in patients who are not helped by their treatment. Consequently, it is important to disentangle which variables do, and which do not, indicate which treatment is better for whom. Apart from demographic variables (e.g., age, gender), 4 potential predictors of treatment effect are identified: introversion, autism, trauma, and sleep. Introversion has been mentioned by client platform MIND [22] as a factor that might interfere with group therapy and should therefore be taken into account in personalizing care. It is conceivable that GST, with its emphasis on sharing feelings and connecting, is less suited for introverted people, which perhaps do better with IST. Autism might also be a barrier to fully participate in social group processes in GST. As a core feature of autism is dysfunction in theory of mind (i.e. understanding emotions, intentions, and other mental processes in other people), social group processes might be especially difficult to follow for participants with autistic features. Regarding trauma, for those who suffered severe levels of childhood abuse and neglect IST might be better suited than GST as there is more time for (individually tailored) extended trauma processing in IST. Finally, sleep problems are increasingly recognized as a factor contributing to maintenance of psychopathology and interfering with psychological treatment [23]. As there is more attention to individual problems such as sleep problems in IST than in GST, IST may have a better effect for those suffering from poor quality of sleep. Identifying predictors of treatment effect could help support clients and clinicians in their decision process as to which treatment might be selected for a given patient.

Despite its wide application in clinical practice, no direct evidence for the (cost)-effectiveness of GST for Cluster-C PDs exists. Before the implementation of this non-validated treatment is further disseminated, it is imperative to investigate the (cost-) effectiveness of GST for Cluster-C PDs. Common practice for assessing this for a new treatment is comparing it to the treatment as usual (TAU) to see whether further implementation is warranted. As GST is hypothesized to be a more cost-effective version of IST, a direct comparison between GST-IST is also desirable. By taking into account several predictors of treatment effect, a more detailed comparison can be made between the 3 therapies in order to gain insight into which treatment works best for whom.

### This study

This paper describes the QUEST-CLC study (QUalitative and Effectiveness study to Select optimal Treatment for CLuster-C PD), a multicenter RCT comparing GST, IST, and TAU for Cluster-C PDs. The main objective of the study is to compare the relative (cost-) effectiveness of these three treatments. Based on previous research, superiority of GST to TAU is expected regarding PD symptom reduction. How GST compares to IST in (cost-) effectiveness is yet unclear. Although in GST larger numbers can be treated in less therapist time than with IST, it is not yet clear how this relates to respective treatment effects. It is hypothesized that GST does not perform worse than IST regarding symptom reduction. As the few previous studies on treatment for Cluster-C PDs that do exist are generally limited to symptom reduction, measures of quality of life, social, work, and other functioning are also included. Furthermore, this study intends to identify predictors and moderators that are relevant for optimal treatment allocation. With such moderators a tool for treatment recommendation will be created. The tool is based on an empirically derived subset of several variables hypothesized to correlate with therapy outcome (i.e., diagnoses, age, gender, ethnic background, socio-economic status, educational level; introversion, autistic traits, sleep problems, severity of childhood traumas).

In addition, two sub studies will be carried out. First, the treatment integrity of GST and IST will be evaluated and compared with TAU. Second, a qualitative study will be performed in which patients and therapists are interviewed. The aim is to obtain a thorough understanding of how the different therapies helped patients recover, what elements are pivotal to lead a fulfilling life, and to explore experiences for patients in the ST-arms, in order to improve ST for Cluster-C patients. Moreover, ST-therapists’ perspectives about treatment will be used to further improve treatment protocols (as was done in the pilot study [24, 25]).

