### Sample size

Sample size calculations were based on symptom reduction effect sizes demonstrated in previous research on GST, TAU, and IST. In our pilot study, a 1-year pre-post effect size of d = 1.24 was found for GST on the primary outcome (severity of the primary PD). There is no data yet of TAU on this index. However, Bamelis and colleagues [12] found a difference between ST and TAU in recovery from PD-diagnosis of OR = 4.073 (81% (ST) vs 52% (TAU)). This is equivalent to an effect size d = .77. Secondly, in a recent multicenter trial, a difference between GST and TAU in reduction of BPD-severity of d = .73 was found [27]. Thirdly, the Svartberg et al. [28] RCT found a 1-year pre-post effect size of psychodynamic treatment, which is one of our TAU treatments, of d = .73 on an index of PD-severity. Taken together, it seems reasonable to assume a (large) pre-post effect size of TAU on PD-severity of d = .8, and also to assume a difference of d = .44 (1.24 – .8) between GST and TAU. Also note that this is a smaller effect size than found between ST and TAU in the Bamelis RCT [12] and between GST and TAU as treatments for Borderline PD [27].

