The power analysis is based on 9 sites, despite 10 sites intent to participate, because sites might withdraw or not reach the intended N. For feasibility purposes a larger N is intended for the GST condition, as more participants can be treated at the same time in a group. With minimal N’s of 162 (GST), 108 (IST) and 108 (TAU) power of pairwise comparisons GST-IST and GST-TAU is 90% at an adjusted p-level of .025 to detect an effect size of d = .44 at post-test (or follow-up). For the GST-IST comparison, we don’t have expectations about the direction of a possible difference, but the power is sufficient to detect a medium effect size. One potential issue is treatment dropout. For pairwise comparisons of GST with the other two arms power is 80% to detect an RR = 2.5 at adjusted p = .025, for instance when dropout is 25% from GST vs. 10% from IST). (G)LMM analysis for repeated measures will be used to account for correlations introduced due to grouping (at multiple levels) and compensate for potential loss of power due to treatment drop-out. This type of analysis usually has greater power compared to non-multilevel/non-repeated measures analyses, however an actual power calculation for multilevel analysis with repeated measures and multiple sites is very difficult if not impossible because of the many random effects of the to-be-estimated model.

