##### Analyses

All analyses are planned to be carried out by SPSS or R statistical software and Excel (for Bootstraps).

Primary and secondary outcomes are analysed with Linear Mixed Models (LMM), with random effect of site. As data of group members are not independent because group members might influence each other, this dependency needs to be taken into account. With the semi-closed group format, groups change in composition every 10 sessions, and participants will share different amounts of time in sessions with group peers: from all group sessions to 10 group sessions. It is plausible to model covariances as a function of the amount of time (i.e., sessions) patients have spent together in a group. This can be achieved in a multilevel model with repeated measures by specifying a Toeplitz covariance structure to model this dependency on the group level. In case this Toeplitz structure turns out to be unsuitable to model the dependency, another (less complex) structure will be specified. For the repeated part at the individual level, the best fitting covariance structure will be chosen (e.g., AR1, ARMA11, Unstructured). If residuals deviate substantially from normal distribution, Generalized LMM (GLMM) will be used with an appropriate distribution (e.g., negative binomial or gamma in case of skewed distributions). All analyses are conducted on the basis of intention-to-treat and will be controlled for initial symptom severity. Dropout from treatment will be analysed with GLMM survival analysis with site as random effect. To take into account participants’ potential influence on each other in group treatment, again a Toeplitz covariance structure will be specified to model this dependency unless a different structure turns out to be more suitable. The three arms will be mutually compared, with a primary interest in the GST-TAU and the GST-IST comparisons. Although the IST-TAU difference is not part of the main research questions, this difference will be analysed exploratively. Tests of predictors and moderators (sleep quality, introversion, autism traits, childhood trauma, verbal intelligence, demographic characteristics) will be done by similar (G)LMM analyses, with the predictor, predictor x time, predictor x treatment, and predictor x time x treatment interactions added to the model.

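### The GST-IST hypothesis is that GST is not worse, but the comparison is planned and powered as a two-sided difference test, which cannot establish that

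*Protocol article*

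**What the plan says.** In the protocol article, the section This study sets out the expectation for group against individual schema therapy: "It is hypothesized that GST does not perform worse than IST regarding symptom reduction". Two sentences earlier the same section calls the relative (cost-)effectiveness of the two treatments unclear.

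The Sample size section treats the comparison differently: "For the GST-IST comparison, we don’t have expectations about the direction of a possible difference, but the power is sufficient to detect a medium effect". It gives one power statement for both pairwise contrasts: "power of pairwise comparisons GST-IST and GST-TAU is 90% at an adjusted p-level of .025", for d = .44 with 162 GST patients and 108 in each other arm. The value .44 comes from the other contrast, since the section says it is reasonable to "assume a difference of d = .44 (1.24 – .8) between GST and TAU".

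The Analyses section plans mixed models on an intention-to-treat basis: "The three arms will be mutually compared, with a primary interest in the GST-TAU and the GST-IST comparisons". The Discussion considers what would follow if GST were found superior to IST or TAU. The article gives no non-inferiority or equivalence margin.

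**The concern.** The hypothesis runs in one direction. It can be supported only by ruling out a GST deficit of some stated size. The planned test asks whether the two arms differ in either direction. If it is not significant, the hypothesis has been neither confirmed nor refuted, and a deficit of clinical interest may still fit the data.

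This affects a main result. GST-IST is the second of the three main questions in the Abstract and a comparison of primary interest in the Analyses section. The Background presents GST as a potentially more cost-effective version of IST, and the Discussion puts its direct delivery cost at about half. A conclusion of similar effect at lower cost would therefore carry weight with policy makers, and the article should be clear about what evidence would justify the first half of it.

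**Working it through.** **Inputs.** GST n = 162, IST n = 108, d = .44, adjusted level .025 (Sample size). The outcome is divided by the baseline SD (Primary outcome measures), so the SD is taken as 1 and differences are in SD units. Clustering, dropout and baseline adjustment are left out of the base calculation.

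**1. The plan's own figure.**
- SE = √(1/162 + 1/108) = 0.1242.
- Two-sided .025: z(.9875) = 2.241. Power = Φ(0.44/0.1242 − 2.241) = Φ(1.30) = 90.3%. The noncentral t calculation gives 90.0%.
- One-sided .025 would give 94.3%.

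The stated 90% is therefore right, and it is the power of a two-sided test for a difference.

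**2. What a non-significant result would mean.** P(non-significant | GST truly worse by δ) = Φ(2.241 − δ/0.1242) − Φ(−2.241 − δ/0.1242). The second term is negligible here.

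| True GST deficit (SD) | P(non-significant) |
|---|---|
| 0.20 | 74% |
| 0.25 | 59% |
| 0.30 | 43% |
| 0.44 | 10% |

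With an assumed baseline correlation of .5, the SE is multiplied by √(1 − .25) = 0.866, giving 0.1076. The 0.30 SD figure then becomes Φ(2.241 − 0.30/0.1076) = 29%.

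**3. Width of the interval.** If the observed difference is zero, the 97.5% CI is ±2.241 × 0.1242 = ±0.28 SD.

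**4. Power to show not worse.** The article gives no margin, so the margins below are assumptions for illustration. Power = Φ(margin/SE − 2.241), with no true difference, at one-sided .0125 (the one-sided equivalent of two-sided .025).

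| Margin (SD) | No baseline correlation | Correlation .5 (assumed) |
|---|---|---|
| 0.30 | 57% | 71% |
| 0.35 | 72% | 84% |
| 0.44 | 90% | 97% |

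The smallest margin with 90% power is (2.241 + 1.282) × SE. That is 0.44 SD without correlation and 0.38 SD with correlation .5.

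**The case against.** The strongest reply is that the article never uses the term non-inferiority. It calls the GST-IST comparison unclear, disclaims direction in the Sample size section, and speaks of possible superiority in the Discussion. On that view the operative sections consistently describe a two-sided comparison, and a single introductory sentence is out of line. This is fair, and it means the article does not show that a non-inferiority design was intended and then mishandled. The conflict between the two sections remains, because a hypothesis that the planned test cannot support is still stated for a comparison of primary interest.

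The statistical analysis plan is not shown and may contain a confidence-interval rule or a margin. The absence of those details is therefore not the point. The article itself fixes the GST-IST sample-size basis as a difference test and disclaims direction, and that conflicts with its own hypothesis whatever the analysis plan adds.

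The test is also not uninformative: it would detect a true deficit of 0.44 SD 90% of the time. The economic evaluation plans bootstrapped cost and effect differences, a cost-effectiveness plane and acceptability curves, none of which needs a margin. Those address the joint cost-effect question but not the clinical claim.

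A reader might infer two stronger points, and the article supports neither:
- *That a p-value above .025 will be taken as confirming the hypothesis.* No section says so. It is a risk left open by a hypothesis without a matching test.
- *That the stated 90% power corresponds only to a margin of .44 SD.* That holds only at one-sided .0125 with no baseline correlation. The analyses are to be controlled for initial severity, which lowers the margin that has 90% power. Group and site clustering, also left out above, would raise it.

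**Conclusion.** The point stands as a mismatch between the stated hypothesis and the planned test. A two-sided difference test at .025 cannot establish that GST does not perform worse than IST. In size, a true GST deficit of 0.30 SD would go undetected about 43% of the time (29% with an assumed baseline correlation of .5), and even an observed difference of zero would leave deficits up to about 0.28 SD within the interval. These figures assume the planned numbers, SD = 1, full data and no clustering.

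The 90% power is not in error for what it describes. It cannot be carried over to a not-worse claim without a margin. The value .44 was derived as the whole expected advantage of GST over TAU and is not offered as a GST-IST margin. The size of any margin is a judgement for the sponsor, and the article gives no basis for a particular value.

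**What to change.** Reconcile the sections This study and Sample size in one of two ways.

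**(a)** Reword the hypothesis as a two-sided question. Report the GST-IST estimate with its confidence interval at the adjusted level, and state that a non-significant result will not be read as showing that GST is not worse. This costs only wording.

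**(b)** Keep the hypothesis. The sponsor then fixes and justifies a non-inferiority margin in baseline-SD units before any outcome data are seen. GST is concluded to be not worse only if the confidence interval at the adjusted level excludes that margin. The GST-IST power is restated for it. The cost is a less favourable stated power if the margin lies below about .38 to .44 SD. No new patients are needed if the lower power is accepted. Restoring 90% power could be expensive: at an illustrative margin of 0.30 SD, one-sided .0125 and no baseline correlation, the IST arm would need (1 + 1/1.5) × (2.241 + 1.282)² / 0.30² ≈ 230 patients, and the GST arm 1.5 × 230 = 345.

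Under either option, align the Discussion's reference to superiority over IST with the choice made.
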